### Randomisation

Participants will be individually randomised on a 1:1:1 ratio, stratified by site, co-resident carer and history of falls, using an independent, secure, web-based, randomisation procedure that can be accessed 24 h a day and held at the NWORTH clinical trials unit, Bangor University [78]. The randomisation system will be maintained by a statistician independent of the analysis and research teams to ensure blinding of allocation and analysis.

### Blinding

A research assistant will perform the randomisation and communicate the allocation to the intervention service provider. Research assistants collecting baseline and follow-up data by questionnaires or telephone will be blind to treatment allocation, and will request participants not to reveal their treatment group. Due to the nature of the intervention, blinding of the intervention is impossible for participants and therapists administering it.

### Baseline data

Pairs of research assistants will administer data collection questionnaires by interviewing participant and carer separately at the participant’s home.

Baseline data will comprise:Demographic and contact details for patient and carer participantsMedical and falls history, including previous fractures, recent hospitalisation and medicationFalls risk factors, including vision and lying and standing blood pressureGross cognition (sMMSE [76], Clinical Dementia Rating [79])CANTAB neuropsychological assessment: Paired Associated Learning (PAL), Attention Switching Task (AST), Spatial Working Memory (SWM) (Cambridge Cognition, Cambridge, UK)Verbal fluency (from MOCA test [75])Scaled outcome variables measuring activities of daily living (ADL) (Disability Assessment for Dementia scale, DAD [80], Nottingham Extended ADL Scale [81]), activity (Incidental and Planned Activity Questionnaire, IPAQ) [82], quality of life (EQ-5D [83], DEMQoL (participant and proxy) [84]), fear of falling (short falls efficacy scale, FES-I [85]), Hospital Anxiety and Depression Scale (HADS) [86], muscle strength (Lafayette dynamometer, Lafayette, IN), Berg Balance Scale [87], Timed Up and Go test [88], SHARE frailty instrument [89].Carer strain (caregiver strain index) [90].Participant and carer service use (Client Service Receipt Inventory, CSRI) [91].

### Intervention

The intervention was developed by a multi-disciplinary team of physiotherapists, occupational therapists, doctors, nurses, psychologists, and patient and public representatives, using the principles of co-production. This was informed by findings from three literature reviews [92–94], clinician, health psychology and neuropsychological expertise ascertained by interview and during workshops, focus group discussions held with patients, carers, and clinicians, and the views of patients and their carers from a prior interview study [62]. Ten patients were treated in a 6-week ‘proof of concept’ study as part of the intervention development, in which intermediate outcomes were measured and field notes were thematically analysed. A comprehensive manual was written, and a training programme devised for physiotherapist, occupational therapist and rehabilitation support worker staff. A therapy workbook was designed to be left in participants’ homes.

The intervention is grounded in established fall prevention expertise, the Assessment of Motor Process Skills activity assessment [95] and theories of motivation (e.g. self-determination theory). It includes a professional assessment of ability, risk and goals. We will use capability-based ‘tailoring’: using assessed neuropsychological impairments, usual level of physical activity, co-morbidities, aligning activities to interests, and assessing priorities through goal-identification and goal-setting. A programme of activities and exercises will be agreed with the patient and carer. Therapy includes functional activity, training and advice, environmental assessment, strength and balance exercises, and dual-task training. The programme will be set out in the participant’s workbook in a format easily accessible to them and their carer. Participants will be encouraged to perform exercises three times per week, and partners, family members or carers will be asked to prompt and support, by telephone if necessary, or to participate as well. The programme will be progressive, intensive and supported by varying intensity of supervision from the research therapists (Fig. 1).

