For the ‘optimising engagement and adherence’ and process evaluations, we will conduct interviews and focus groups. We will undertake three small focus groups with patients with mild dementia, and their family carers, each comprising three to five participants to investigate promotion of adherence. In the process evaluation, we will conduct semi-structured interviews with about ten participants in each active-treatment arm (moderate- and high-intensity supervision). Carers will be interviewed separately or together with the participant, depending on their preference. We will select for interview participants with low- and high-adherence, identified through their exercise diaries, self-report or therapist-report. We will also seek to interview a sample of participants who discontinue the intervention (up to 10, and their carers). We will undertake two to three staff focus group discussions, each of six to eight members.

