#### Falls and activity

Study-related and other activity will be quantified by time using the daily diary. Falls and injurious falls will be counted. Participants will be asked to wear pedometers in weeks 1, 26 and 50 as an objective measure of activity.

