#### Process evaluation, motivation and adherence study

We will record the number of therapy sessions delivered. We will estimate amount of exercises and prescribed activities done independently using the daily diary.

Data on habit formation will be collected at alternate months by telephone, using a standardised scale, the Self-Reported Habit Index [99].

At months 1, 3 and 6 data on participant’s and staff perceptions of motivational communication will be collected by telephone, using the Healthcare Climate Questionnaire, adapted for exercise settings [100, 101].

Central to self-determination theory is the concept of basic psychological needs [102]. These needs (for competence, autonomy, and relatedness) must be satisfied for people to develop and function in healthy or optimal ways [103]. We will record psychological variables hypothesised to be related to adherence at baseline and follow-up:Behavioural Regulation in Exercise Questionnaire (BREQ-2) [104]Basic Psychological Need Satisfaction and Frustration Scale [105] (participants and staff)Clinician’s work motivation (Work Extrinsic and Intrinsic Motivation Scale) [106].

Qualitative interviews will take place at home. Therapists and their assistants delivering the intervention will take part in focus group discussions, with an experienced facilitator, held at a convenient location. Interviews and focus group discussions will be audio-recorded. We will ask about: the experience of undertaking the programme; perceived benefits or value; difficulties, barriers, and facilitators; mechanisms of behaviour change and habituation to the exercise regime; the impact of supervision intensity and other factors on acceptability and adherence; and whether level of supervision can be matched to individual participant characteristics; reasons for high- or low-levels of adherence, or discontinuation of the programme; the acceptability of carer support; and the extent of burden this might impose.

Thirty purposively-selected therapy sessions will be video-recorded, to include a range of clinicians and stages of the intervention.

The experience of delivering the intervention will be explored in focus groups with staff. We will discuss: adequacy of the training; the experience of delivering the intervention; perceptions of patient and carer responses; perceived effectiveness; barriers to implementation and how these may be overcome.

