### Statistics and data analysis

#### Feasibility analysis

The main analysis will be of feasibility outcomes. We will calculate:Recruitment rate (randomisations per month)Retention rate (proportion completing therapy programme and study follow-up)Therapy adherence rate (proportion of professionally-supervised visits undertaken, and time spent doing self-directed therapeutic exercise or activity)Missing data (proportion fully completed, for each scale, at each time point).

Participant throughput and flow will be summarised for each trial arm using a CONSORT diagram. Reasons for non-eligibility, non-treatment, withdrawals and non-completion of questionnaires will be reported.

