#### Optimising uptake and adherence

Using the Capability, Opportunity, Motivation – Behaviour (COM-B) framework [58], we will seek evidence on what support participants would like, or will need, to achieve short- and long-term adherence. We will review methods to support uptake and adherence in exercise interventions reported in the literature, drawn from a variety of conditions, which might be adapted or used for people with dementia. We will develop a strategy for promoting and supporting uptake, adherence and persistence with the intervention, develop guidance on tailoring, need for direct supervision, and describe habit formation and factors that predict successful adherence.

We will analyse baseline distributions, changes and associations with psychological variables hypothesised to determine motivation and adherence, including motivation of participants to exercise (BREQ-2 [102]), and basic psychological needs, [105], and clinician factors, including communication style [100]), work motivation [106], and basic psychological needs [105].

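### Self-directed adherence is defined as time spent, with no denominator, so it measures dose; adherence to the three-times-a-week target should be reported beside it

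*Protocol article*

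**What the plan says.** The Feasibility analysis section gives the therapy adherence rate two parts. The supervised part is a proportion: "proportion of professionally-supervised visits undertaken". The self-directed part is an absolute quantity: "time spent doing self-directed therapeutic exercise or activity". Two other sections point the same way. Under Falls and activity, "Study-related and other activity will be quantified by time using the daily diary". Under Process evaluation, motivation and adherence study, "We will estimate amount of exercises and prescribed activities done independently using the daily diary".

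The Intervention section describes an individual prescription: "We will use capability-based ‘tailoring’: using assessed neuropsychological impairments, usual level of physical activity, co-morbidities", with interests and goals also taken into account. The programme is agreed with patient and carer, written into a workbook and made progressive. The one quantity set for everyone is a frequency: "Participants will be encouraged to perform exercises three times per week". No session length is stated.

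Adherence is then used in three places. Under Participants: "We will select for interview participants with low- and high-adherence, identified through their exercise diaries, self-report or therapist-report". Under Optimising uptake and adherence, the team will "describe habit formation and factors that predict successful adherence". The Discussion makes the choice of arm for the definitive trial, or the way supervision is tailored, depend critically on how well long-term adherence is established.

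**The concern.** Adherence is the share of what was asked that was done. The supervised component has that form and the self-directed component does not. Where programmes differ between people, minutes recorded depend on the amount set as well as on the share completed, and the amount set is shaped by impairment, usual activity and comorbidity. Those same characteristics may then appear to predict adherence when they only predict the prescription. Progression can do the same within one person, so that minutes rise while the share done falls.

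Adherence is one of the named feasibility outcomes and feeds the design of the definitive trial. With 60 participants over three arms and about ten interviews per active arm, a few people put in the wrong adherence group would be noticeable.

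**Working it through.** **No figure to reproduce.** The article gives no expected minutes, session lengths or adherence level. The check is therefore of the definition, with assumed values to show how it behaves.

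**Identity.** Minutes per week = 3 × L × s, where 3 is the stated weekly frequency, L the minutes asked for per session (not stated, assumed) and s the share completed.

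**When does the order reverse?** Compare A, who does everything asked (s = 1), with B, who does half (s = 0.5). B records more minutes when 0.5 × L(B) > L(A), that is, when L(B)/L(A) > 2.

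| L(A) | L(B) | A, all done | B, half done | Order by minutes |
|---|---|---|---|---|
| 20 | 30 | 60 | 45 | correct |
| 15 | 30 | 45 | 45 | tie |
| 15 | 40 | 45 | 60 | reversed |
| 20 | 60 | 60 | 90 | reversed |

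**Within one person.** At 15 minutes with all done, 3 × 15 × 1.0 = 45. After progression to 45 minutes with half done, 3 × 45 × 0.5 = 67.5. Recorded time rises by half while the completed share halves.

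**Size under assumptions.** Let L have mean 1 (rescaled) and coefficient of variation c, and let s have mean 0.6 and SD 0.25, independent of L. Then

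- Var(L × s) = (1 + c²)(0.6² + 0.25²) − 0.6²
- r(minutes, share) = 0.25 / SD(L × s)
- r(minutes, prescription) = 0.6c / SD(L × s)

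At c = 0.4: 1.16 × 0.4225 − 0.36 = 0.1301, so the SD is 0.361. The correlation of minutes with the share is 0.25/0.361 = 0.69, and with the prescription 0.24/0.361 = 0.67.

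A simulation of 400,000 draws (lognormal L, beta s) agrees and adds the fraction of the top third by minutes that is not in the top third by share:

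| c | r(minutes, share) | Top third misplaced |
|---|---|---|
| 0.1 | 0.97 | 12% |
| 0.2 | 0.89 | 23% |
| 0.4 | 0.69 | 35% |
| 0.6 | 0.54 | 42% |

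With an SD of 0.20 for the share, the correlation runs from 0.85 (c = 0.2) to 0.47 (c = 0.6). If c = 0, so that everyone is asked for the same length at all times, minutes are proportional to the share and there is no distortion.

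**With a frequency denominator.** If A does 3 of 3 sessions and B averages 1.5 of 3, they score 100% and 50% whatever the session lengths.

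**The case against.** The strongest reply is that the article prescribes no minutes. Tailoring and progression could act on the type or difficulty of exercise and leave session length alike for all, in which case time spent would track adherence well. This stands: the distortion is conditional, and the coefficients of variation above are assumptions with no source in the article.

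The harm to later uses can also be overstated. A reader might infer that interviewees will be ranked by minutes, or that minutes will be the dependent variable in the predictor work. The article says neither. Interview selection may also use self-report or therapist-report, and a therapist can judge a participant against the agreed programme. The measure of successful adherence in the predictor work is left open. Adherence is also approached by other routes: sessions delivered, a habit scale, pedometers, and persistence at 18 and 24 months. Minutes are also worth having, since the process evaluation wants dose.

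A last reply is that scoring detail belongs in the full protocol or analysis plan. That is true of detail, but here the article itself states the measure, and under the name of an adherence rate. One could parse the phrase as a proportion of time, but no total or prescribed time is named, and the two other sections quoted speak of time and amount. The missing denominator therefore stands.

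**Conclusion.** The point holds in a limited form. The self-directed component of the adherence rate, as stated, is a dose without a denominator, although the programmes are individually tailored and progressive and a common weekly target is available. If session length varies between people or over time, minutes blend prescription with adherence and can misorder participants. That bears on the predictor work, the diary-based part of interview selection and the choice of arm.

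The size in this trial is unknown. The correlations of 0.89 to 0.54 rest on assumed inputs and on independence of prescription and completed share.

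A reader might go further and conclude that fully adherent frail participants will be scored below half-adherent fit ones. The article does not support that: it would need prescribed lengths more than twofold apart, and no lengths are given. The supervised component is unaffected. This is worth correcting because adherence is a named feasibility outcome and the correction is cheap; it does not undermine the trial.

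**What to change.** In the feasibility analysis, keep self-directed minutes but label them as dose, and add adherence to the frequency target from the daily diary:

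- **Overall exercise adherence:** supervised plus independent exercise sessions in the week, divided by three.
- **Independent adherence:** independent sessions divided by the sessions remaining after that week's supervised exercise sessions. A week with three or more supervised exercise sessions has no remainder and is left out of this ratio.

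The two must be kept apart. The high-intensity arm has a support worker twice a week for the first three months. If those visits include exercise, a participant who does nothing alone scores 2/3 = 67% on the first ratio and 0/1 = 0% on the second. Counting supervised sessions as self-directed would favour that arm and would count again visits already in the supervised component.

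Where the workbook in force at the time records a duration, minutes done over minutes set can be given as a supplement; it would also show shortened sessions, which a session count does not. Use the ratios alongside minutes in the predictor work and when diaries are used to pick low and high adherers.

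The cost is mainly analysis wording, as diary and workbook already exist. Two limits remain. Sessions or exercise days must be countable from the diary, which should be confirmed. The target covers exercises only, so other prescribed activity stays reported as time.

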**Fig. 1 Fig1:**
[figure not shown]
Overview of assessment and intervention. *PT* physiotherapist, *OT* occupational therapist, *GP* general practitioner/family doctor, *wk.* week

The control arm will be the offer of a standard falls assessment and advice completed by a therapist, with up to two follow-up visits if thought clinically necessary.

The moderate-intensity supervision arm participants (3-month programme) will receive a total of 11 treatment sessions: 6 from an occupational therapist (OT) and 5 from a physiotherapist over 12 weeks. Participants will be expected to exercise and complete activities independently between supervised sessions, and taught to continue after the supervision period has stopped. The moderate-intensity intervention was modelled on the intervention in an ongoing Australian trial [96, 97].

The higher-intensity supervision arm (12-month programme) will comprise 11 treatment sessions from registered therapists: 6 from an occupational therapist, 5 from a physiotherapist plus supervised support from a rehabilitation support worker (RSW) twice a week for 3 months, once a week for 3 months, once a fortnight for 3 months, and once a month for 3 months. In total they will get 51 treatment sessions, and will be asked to continue with the intervention programme independently as supervision tapers. At initial, review and progression points, the RSW will visit jointly with the therapists.

**Fig. 2 Fig2:**
[figure not shown]
Schedule of enrolment, interventions and assessments

The feasibility and practicability study, and associated process evaluation, forms part of the development process for the intervention, which will be subject to further refinement based on the findings. For this reason, we will not publish the manual until the intervention is finalised (anticipated September 2018).

### Follow-up

Researchers will visit participants at home at 12 months (± 2 weeks) to complete health status assessments by interview with the participant and informant. Participants will keep a daily diary for 12 months, detailing activities and exercises undertaken and recording falls. This will be supported and prompted by monthly telephone calls [98]. Measures will be taken to ensure that falls ascertainment is not biased across the intervention arms (e.g. therapists or RSWs will be asked not to prompt recall of falls). Health and social care use will be ascertained during the telephone calls, using electronic healthcare records and the Client Service Receipt Inventory (CSRI) at follow-up interview. Persistence with the therapy programme, health and social care use, and hospitalisation will be ascertained by short questionnaire at 18 and 24 months.

### Outcome measures

#### Trial feasibility outcomes

The feasibility outcomes are recruitment, retention, adherence and acceptability of the intervention, and completion of baseline and outcome data. A recruitment log will be maintained, and recruitment and withdrawal rates recorded.

#### Health status outcome measures

Disability Assessment for Dementia (DAD) ADL scale [80]Nottingham Extended ADL scale [81]IPAQ activity questionnaire [82]CANTAB neuropsychological assessment: Paired Associated Learning (PAL), Attention Switching Task (AST), Spatial Working Memory (SWM)Verbal fluencyDEMQoL and EQ-5D quality of life questionnaires [83, 84]Short falls efficacy scale (fear of falling, FES-I) [85]Hospital Anxiety and Dementia Scale (HADS) [86]Berg balance Scale [87]Single- and dual-task Timed up and Go (TUG) test [88]SHARE frailty instrument [89]Muscle strength (Lafayette dynamometer)Resting and post-exercise pulse rate.Carer strain [90]

#### Falls and activity

Study-related and other activity will be quantified by time using the daily diary. Falls and injurious falls will be counted. Participants will be asked to wear pedometers in weeks 1, 26 and 50 as an objective measure of activity.

#### Process evaluation, motivation and adherence study

We will record the number of therapy sessions delivered. We will estimate amount of exercises and prescribed activities done independently using the daily diary.

Data on habit formation will be collected at alternate months by telephone, using a standardised scale, the Self-Reported Habit Index [99].

At months 1, 3 and 6 data on participant’s and staff perceptions of motivational communication will be collected by telephone, using the Healthcare Climate Questionnaire, adapted for exercise settings [100, 101].

Central to self-determination theory is the concept of basic psychological needs [102]. These needs (for competence, autonomy, and relatedness) must be satisfied for people to develop and function in healthy or optimal ways [103]. We will record psychological variables hypothesised to be related to adherence at baseline and follow-up:Behavioural Regulation in Exercise Questionnaire (BREQ-2) [104]Basic Psychological Need Satisfaction and Frustration Scale [105] (participants and staff)Clinician’s work motivation (Work Extrinsic and Intrinsic Motivation Scale) [106].

Qualitative interviews will take place at home. Therapists and their assistants delivering the intervention will take part in focus group discussions, with an experienced facilitator, held at a convenient location. Interviews and focus group discussions will be audio-recorded. We will ask about: the experience of undertaking the programme; perceived benefits or value; difficulties, barriers, and facilitators; mechanisms of behaviour change and habituation to the exercise regime; the impact of supervision intensity and other factors on acceptability and adherence; and whether level of supervision can be matched to individual participant characteristics; reasons for high- or low-levels of adherence, or discontinuation of the programme; the acceptability of carer support; and the extent of burden this might impose.

Thirty purposively-selected therapy sessions will be video-recorded, to include a range of clinicians and stages of the intervention.

The experience of delivering the intervention will be explored in focus groups with staff. We will discuss: adequacy of the training; the experience of delivering the intervention; perceptions of patient and carer responses; perceived effectiveness; barriers to implementation and how these may be overcome.

